### Outcomes

#### Mammographic breast density: primary outcome in part 1

Full-field digital mammography at baseline and after 12 months of treatment comprises mediolateral oblique and craniocaudal views of both breasts. Abnormalities will be evaluated on both views of each breast. In addition to visual judgement, a computer-based quantitative assessment will be performed. All mammograms will be pseudonymised so that the assessor will be unaware of the patient’s identity and type of treatment. The dense area on the right craniocaudal view image will be measured by using a commercial computer-assisted programme. A computer then records the number of pixels that fall within the defined areas according to the methodology described and used by us previously.^27^,^30^ Percentage change in mammographic density will be evaluated and compared between groups.

#### Breast cell proliferation: secondary outcome in part 1

Core needle breast biopsy from the upper lateral quadrant of the right breast will be taken after local anaesthesia at baseline and after 12 months of treatment. Ultrasound is used to identify areas with fibroglandular tissue. All women will be biopsied at the Mammography unit, Karolinska University Hospital. Tissue samples are paraffin-embedded and sectioned at 5 µm until analysis. Slides will be stained for the proliferation marker Ki-67 and other markers related to proliferation and apoptosis (caspase-3, p53 and bcl-2), and steroid hormone receptors. In addition to standard immunohistochemistry, a quantitative image analysis will be performed using a Leica microscope and Sony video camera connected to a computer with an image analysis system (Leica Imaging System, Cambridge, UK).^27 31^ Percentage change in breast cell proliferation will be evaluated and compared between the groups.

#### Endometrial assessment: secondary outcome in part 1 and primary outcome in part 2

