### Sample size calculation

#### Mammographic breast density: primary outcome in part 1

Based on data from the WHI study, it was shown that an increase in mammographic density by 1% during combined MHT corresponded to a 3% increase in risk of breast cancer.^42^ We estimated that a difference of at least 30% in treatment response between the groups would be clinically relevant. A power analysis based on our previous results,^27^,^30^ and assuming a 35% difference in treatment response, revealed that a patient material of 91 women/group would be sufficient to detect a significant difference in mammographic breast density between the groups at the 5% level (two sided) with 80% power. Considering the estimated rate of discontinuation and incomplete data (~30%), the target sample for this part of the study would be 260 patients.

#### Endometrial pathology: primary outcome in part 2

The reported 1-year background incidence rate for endometrial hyperplasia/cancer in postmenopausal women treated with authorised oestrogen/progestogen combinations is approximately 0%–1%.^18 19^ With a sample size of 300 women in the treatment arm mP+E, two or less women with serious adverse endometrial outcomes would result in an annual incidence of 0.67% or less with an upper bound of the one-sided 95% CI of 2.08% or less. Considering the estimated rate of discontinuation and incomplete data (~30%), the target sample for this part should be 390 patients, 130 women randomised to mP from part 1 and another 260 women from part 2.

The total number of patients in part 1 (n=260) and part 2 (n=260) will be 520.

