#### Statistical analysis

Analyses of primary and secondary outcomes will be based on an intention-to-treat (ITT) population (all subjects who have received at least one dose of study drug with a baseline evaluation meeting the entry criteria), as well as per-protocol population (subjects who have completed the study without major protocol deviations). The safety analysis population will comprise all patients who received at least one dose of the study drug.

The primary outcome variable mammographic breast density (part 1), expressed as percentage, will be compared between and within groups using the mixed model procedure with subjects as a random factor, and treatment (mP+E and NETA+E), time (baseline and exit) and treatment×time as fixed factors. Differences between groups will be evaluated by the interaction treatment×time, and differences within groups by the factor time, by holding the other factor (treatment) fixed.

Incidence of endometrial pathology (hyperplasia or cancer) in the mP+E group as endometrial safety (part 2) and based on histopathology will be expressed as incidence rate and 95% CI, in line with the European Medicines Agency guidelines.^43^

The secondary outcome variables (breast cell proliferation, endometrial cell proliferation, endometrial thickness using ultrasound, gene and protein expression of growth factors and apoptosis markers in breast and endometrial tissue, vaginal and gut microbiome, blood levels of serum hormones, growth and metabolic factors, lipid profile, and coagulations factors) will be analysed using the mixed model procedure with the same factors as above. In case of positively skewed distributions of these variables, log transformation will be performed prior to the analysis.

The Mann-Whitney U test will be used to compare the groups with respect to the changes in the PHQ-9, HADS, PGWB and WHQ and the Wilcoxon matched pairs test for changes in these variables within the groups.

If missing data occur in the ITT analysis, the method last observation carried forward (LOCF) will be used. Assuming missing data occur at random, patients with missing data can be included in the mixed model analysis, otherwise, we use the LOCF procedure. Correlations will be assessed by Spearman’s rank correlation test. A p<0.05 will be considered significant.

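### The LOCF fallback for mammographic density depends on an untestable assumption and, with only two mammograms, sets any missing change to zero

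*Protocol article*

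**What the plan says.** The Statistical analysis section of the protocol article gives two consecutive statements on missing data. The first is unconditional: "If missing data occur in the ITT analysis, the method last observation carried forward (LOCF) will be used". The second makes the method depend on the missingness mechanism: "Assuming missing data occur at random, patients with missing data can be included in the mixed model analysis, otherwise, we use the LOCF procedure".

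The primary model for part 1 is a mixed model with subject as a random factor and treatment, "time (baseline and exit) and treatment×time as fixed factors"; the interaction carries the between-group comparison. The Outcomes section confirms that there are two measurements: "Full-field digital mammography at baseline and after 12 months of treatment". The intention-to-treat set is "all subjects who have received at least one dose of study drug with a baseline evaluation meeting the entry criteria", so it includes women with no exit mammogram.

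On effect size, the Sample size calculation section says "We estimated that a difference of at least 30% in treatment response between the groups would be clinically relevant", and the power analysis proceeds by "assuming a 35% difference in treatment response". It allows about 30% for discontinued and incomplete cases together. The section on discontinuing study treatment plans end-of-study assessments for every dosed woman who stops early. According to Table 1 and the end-of-treatment section, these include a second mammogram in part 1.

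**The concern.** There are two linked problems.

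First, the primary method is not fixed. Whether data are missing at random cannot be established from the observed data, and the article gives no criterion for deciding. The choice between mixed model and LOCF could therefore be made after results are seen.

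Second, with one baseline and one exit value there is no intermediate density to carry forward. LOCF becomes baseline carried forward: a woman without an exit mammogram enters with zero change, treated as measured. The article's own Discussion cites evidence that hormone treatment alters density within weeks, so zero change is a strong assumption. The clause invokes LOCF exactly when missingness is thought not to be at random, a situation LOCF does not repair. The mixed model already accepts women with a baseline value only, so LOCF is not needed to keep them in the analysis.

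At stake are bias in the primary estimate and, if missingness differs by arm, a difference produced by the imputation alone.

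**Working it through.** **Reproducing the plan's figure.** 91 evaluable women per group and a 30% allowance give 91 / 0.70 = 130 per group, 260 in total, as stated. The 91 cannot be derived because no SD is given. Working back from two-sided 5% and 80% power, the standardised effect is (1.960 + 0.842) × √(2/91) = 0.415. If the difference is 35 units, the SD is 35 / 0.415 ≈ 84.

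**Attenuation with equal missingness.** Let a share *m* of each arm lack an exit mammogram, unrelated to response, and read 35% as an absolute difference in mean change. With zeros imputed, the expected LOCF difference is 35 × (1 − *m*):

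| *m* | LOCF difference |
|---|---|
| 5% | 33.3 |
| 10% | 31.5 |
| 14.3% | 30.0 |
| 20% | 28.0 |
| 30% | 24.5 |

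The break-even against 30 is *m* = 1 − 30/35 = 14.3%.

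**Relative reading.** Suppose 35% is relative, for example mean changes of 40 and 0.65 × 40 = 26. Equal zero imputation at 30% gives 28 and 18.2. The ratio is unchanged (1 − 18.2/28 = 35%); only the absolute gap shrinks, from 14 to 9.8.

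**Power.** With SD 84, 130 per arm and *m* = 30%, the variance in an arm with mean change μ is (1 − *m*)SD² + *m*(1 − *m*)μ². For assumed arm means of 0 and 35, power under LOCF is 79.0%; for 10 and 45 it is 78.3%. With 91 completers per arm it is 80%.

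**Unequal missingness, true difference 35.** The LOCF difference is μ_NETA(1 − m_NETA) − μ_mP(1 − m_mP). With 20% missing on mP and 40% on NETA, assumed mP/NETA means of −10/25, 0/35 and 10/45 give 23, 21 and 19. With the rates reversed they give 26, 28 and 30.

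**Unequal missingness, no true difference.** Assume both arms rise by δ = 0.5 SD of change, with 130 per arm. In SD units, an arm's LOCF mean is (1 − *m*)δ and its variance (1 − *m*) + *m*(1 − *m*)δ².

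- 25%/35%: the means are 0.375 and 0.325, a false difference of 0.05. The SE is √((0.797 + 0.707)/130) = 0.108, a shift of 0.46 SE. Rejection is about 7.5% (7.7–7.8% in simulations of 20,000 trials).
- 20%/40%: the means are 0.40 and 0.30, a false difference of 0.10. The SE is √((0.84 + 0.66)/130) = 0.107, a shift of 0.93 SE. Rejection is about 15.4% (15.4–15.6% simulated).
- 30%/30%: no false difference; 4.9–5.0% simulated.

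The result is sensitive to the assumed rise. At 20%/40%, rejection is 7.9% for a 0.25 SD rise and 40% for a 1 SD rise.

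**The case against.** The two sentences need not conflict. The second can be read as qualifying the first, giving the mixed model under missing at random and LOCF otherwise. The LOCF sentence also follows the paragraph on questionnaires, which are collected at 3, 6 and 9 months as well and so offer later values to carry forward. This softens the charge of contradiction. It does not remove the fallback, because the conditional sentence names the mixed model, which is the density analysis.

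Several stronger readings are tempting, but the documents do not support them:

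- **A reader might infer that about 30% of women will be given zero change and that 24.5% is the expected result.** The 30% combines discontinuation with incomplete data, and early stoppers are due an exit mammogram, so fewer may be missing. The 24.5% is the far end of that allowance, on the LOCF branch and on an absolute scale that the article does not specify.
- **A reader might infer that an estimate below 30% means a failed trial.** The 30% is planning rationale; the analysis tests the interaction at 5% and sets no threshold at 30%.
- **A reader might infer a serious loss of power, or an invalid test even with balanced missingness.** Power moves by one to two percentage points, and null rejection at 30%/30% stays at 5%.
- **A reader might infer that an inflated type I error is to be expected.** The arm-specific rates and the 0.5 SD rise are assumptions. The trial is double-blind, and nothing in the article predicts a 10 to 20 point gap in missingness.

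Finally, the details of a sensitivity analysis commonly sit in an analysis plan, which is not shown. Their absence is not the defect; the stated LOCF rule is.

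**Conclusion.** The point holds in a limited form. The stated rule leaves the primary missing-data method dependent on an unverifiable assumption. Its fallback imputes zero change for a two-time-point outcome in the one situation it cannot address. Neither conclusion depends on the numerical assumptions.

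The size is conditional. With equal missingness and an absolute 35% difference, the estimate drops below 30% once more than about 14% of women lack an exit mammogram, and to about 24.5% at the full allowance. With a relative difference and equal missingness, the ratio is unaffected. The harm is bias rather than lost power. A false-positive risk of about 8% to 16% arises only if missingness differs by arm and density rises in both, under the assumed rates and rise.

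**What to change.** Remove LOCF for mammographic density. State one primary rule: the likelihood-based mixed model fitted to all observed baseline and exit densities, including exit mammograms obtained after early stopping, with no single imputation. Replace the clause that falls back to LOCF with a prespecified sensitivity analysis for data missing not at random, such as delta-adjusted multiple imputation. Settle this before unblinding.

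The cost is a change of analysis wording and one additional sensitivity analysis. Visits, procedures and sample size are unaffected.

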### Randomisation

In part 1, patients will be randomised (in a 1:1 ratio) to 12 months of study treatment. The randomisation list will be created electronically using random permuted blocks with a random block size of a maximum of 6. This will be carried out by Apotek Produktion & Laboratorier and kept at the Karolinska University Hospital pharmacy. All personnel involved directly in the study shall be unaware of the treatment assigned until study closure and completion of analyses. Mammography examinations will be performed at different centres; however, evaluation of mammograms will be performed centrally by independent specialists blinded to treatment. Collection of breast biopsies will be performed only at Karolinska University Hospital. As no effect of centres is assumed, randomisation will be pooled over the centres.

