#### Vaginal and gut microbiome: secondary outcome

Vaginal and rectal microbiome will be characterised based on shotgun metagenomic sequencing and metabolomic profiling. DNA extraction will be performed with standardised and automated pipelines for vaginal^35^ and rectal samples.^36^ Taxonomical profiling will be based on metagenomic sequencing to identify important organisms on species/strain level as well as to characterise their functional information such as enzymes involved in metabolic pathways and antibiotic resistance. Untargeted metabolomic analysis of vaginal and rectal samples will be carried out using ultrahigh performance liquid chromatography-tandem mass spectroscopy.^37^ The absolute and relative abundance of different microbial species and diversity in the women before and after 12-month treatment will be evaluated and compared between groups.

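### The single p<0.05 rule also covers the high-dimensional microbiome outcome, where about 5% of null features would be declared treatment effects

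*Protocol article*

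**What the plan says.** In the protocol article, the Statistical analysis section lists secondary variables that "will be analysed using the mixed model procedure with the same factors as above", meaning treatment, time and their interaction. The vaginal and gut microbiome is on that list. The section ends with "A p<0.05 will be considered significant". No outcome is exempted, and nothing says that the p-values are adjusted.

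The section on the vaginal and gut microbiome shows what that list entry contains. Taxonomy comes from shotgun sequencing, down to species or strain, with functional information such as enzymes and antibiotic resistance. "Untargeted metabolomic analysis of vaginal and rectal samples will be carried out". The quantities compared between groups are the "absolute and relative abundance of different microbial species and diversity". The section heading calls the outcome secondary, not exploratory.

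The sample size section uses the 5% level for one test, mammographic density in Part 1: "at the 5% level (two sided) with 80% power".

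**The concern.** A 5% threshold suits one pre-specified comparison, or a short list that a reader can weigh item by item. It does not suit an assay that produces one test per species, pathway or metabolite. The number of false findings then grows in proportion to the number of features measured, and a list of significant organisms or metabolites will appear whether or not the two progestogens differ.

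The comparison is randomised and double-blind, so differences found in this way would carry more credibility than they deserve. The article plans to communicate results through journals, social media and patient organisations, and hopes that they will inform guidelines.

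This is a matter of what the article states, not of what it leaves out. It names both the model and the decision rule for this outcome, and an analysis plan that used false discovery control would have to qualify the published rule.

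**Working it through.** **Inputs from the article.** The significance threshold is 0.05, without stated adjustment (Statistical analysis). The model is the same mixed model for each listed variable (same section). The features are species- or strain-level taxa, functional features and untargeted metabolites at two sites (microbiome section). The number of features, m, is not stated, so it is an assumption and a range is shown.

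**The plan's own figure.** The article gives no expected number of false positives to reproduce. The figure closest to the 5% level is the Part 1 sample size. The article says that a power analysis "revealed that a patient material of 91 women/group would be sufficient". With 30% loss, 91 / (1 − 0.30) = 130 per group, and 2 × 130 = 260, which matches the stated target. That calculation serves one density test and does not extend to the microbiome features.

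**Expected false positives.** If m features are truly null and each test holds its nominal level, the expected number declared significant is 0.05 × m. If the tests are independent, the chance of at least one is 1 − 0.95^m. The ranges below are binomial 95% ranges under independence.

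| Assumed null features m | Expected 0.05 × m | 95% range | Chance of at least one |
|---|---|---|---|
| 100 | 5 | 1 to 10 | 0.994 |
| 500 | 25 | 16 to 35 | effectively 1 |
| 1,000 | 50 | 37 to 64 | effectively 1 |
| 5,000 | 250 | 220 to 281 | effectively 1 |

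**Correlated features.** Species and metabolites are not independent. Correlation leaves the expected count unchanged but widens its spread. In a simulation with m = 1,000, blocks of 20 and within-block correlation 0.5, the mean was 50 and the 95% range was 27 to 78, against 37 to 64 under independence. At least one false positive occurred in every simulated data set.

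**What the count leaves out.** It allows one between-group test per feature. The section also plans within-group tests over time and two analysis populations (intention-to-treat and per-protocol). These overlap with the first test, but each is a further route to p<0.05.

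**What the replacement would do.** Benjamini-Hochberg at 5% orders the m p-values in a family and finds the largest k whose k-th smallest p-value is at most 0.05 × k / m. At m = 1,000, a lone finding would need p ≤ 0.05 / 1,000 = 0.00005. The expected false share among declared findings is then at most 5% within the family, for independent or positively dependent tests. Control is per family: with four independent, wholly null families, the chance of at least one declared feature somewhere is about 1 − 0.95^4 = 0.185. That is a reason to label the results exploratory as well.

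**The case against.** The strongest reply is that this is only an omission. False discovery procedures, feature filtering and normalisation commonly sit in an analysis plan or a separate omics plan, neither of which is shown, and a 0.05 threshold could be applied to adjusted p-values. The first half is fair: such a plan may exist. But the rule as published is unqualified and covers an outcome that the same section names, so a reader following the article would test each feature at 5%.

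A second reply is that feature-by-feature testing is partly inferred. The Statistical analysis section does not name metabolomics. The outcome section speaks of important organisms and also of diversity, which is a low-dimensional summary. This stands in part: metabolites enter only because the outcome section makes them part of the microbiome outcome, and the text does not say that every species will be tested. It does say that the abundance of different species will be compared between groups, which is enough for the concern.

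Several stronger readings are tempting, but the article does not support them:

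- **That the rule will produce dozens or hundreds of false effects.** This depends on a feature count that the article does not give. An expected 24 needs 24 / 0.05 = 480 null features, and an expected 200 needs 200 / 0.05 = 4,000.
- **That every secondary outcome goes through this mixed model.** The questionnaires have the Mann-Whitney and Wilcoxon tests, and bleeding pattern is not on the mixed-model list.
- **That the tissue markers form another high-dimensional panel.** Those named, such as Ki-67, caspase-3, p53 and bcl-2, make a short targeted list.
- **That log transformation fails because some species have zero counts.** The handling of zeros is an implementation detail that the analysis plan can settle.

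**Conclusion.** The concern holds for the high-dimensional part of the microbiome outcome. The article fixes a decision rule under which about 5% of null features would be called treatment effects. The expected number is 5 at 100 features and 250 at 5,000. These counts assume that all m features are null and that each test holds its nominal level, and m itself is assumed. If some features truly differ, 0.05 is multiplied by the number that do not. The near-certainty of at least one false finding at 100 features (0.994) assumes independence.

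The reach is limited. The Part 1 primary comparison is one interaction test, and Part 2 reports an incidence with a confidence interval; neither is affected. The microbiome is a secondary outcome for which the article makes no power claim. The point is worth correcting because the remedy is nearly free, but it does not threaten the trial's main conclusions.

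**What to change.** Add to the Statistical analysis section, or to the analysis plan with a note that it qualifies the published rule:

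- The p<0.05 rule does not apply feature by feature to the high-dimensional outcomes.
- The families are vaginal species, rectal species, vaginal metabolites and rectal metabolites, plus functional features if they are tested.
- Within each family, significance is declared by Benjamini-Hochberg at a 5% false discovery rate, and the number of features tested is reported.
- These results are labelled exploratory.

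The targeted tissue markers and the other secondary outcomes need no change on this account. The treatment of zeros, and any compositional transformation for relative abundances, can be left to the analysis plan.

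The cost is a few sentences and routine code, with no effect on participants or sample size. The downside is that fewer features will be nominally significant, and some modest true differences may not be declared.
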